|  | Synopsis, Section 5.2                                                                                            | Removed the stated requirement “Does not meet all inclusion criteria” from the inclusion criteria.                                                     | Condition removed as redundant.                                                                                                                              |
|  | Table 4-1                                                                                                        | Removed scheduled ECGs between Screening and EOS/ET                                                                                                    | ECGs during treatment judged to be unnecessary for healthy subjects being administered an approved drug.                                                     |
|  | Section 6.6.1                                                                                                    | Clarification of birth control restrictions for subjects at Screening.                                                                                 | Text revised to clarify requirements for birth control use prior to Screening if Screening occurs less than 30 days prior to the initial CRU admission.      |
|  | Synopsis, Section 3.2                                                                                            | Specified that secondary endpoints “will include:”, revised from “may include:”; Addition of Cmax on Day 3 across all 6 doses as a secondary endpoint. | Endpoints were revised to address FDA feedback.                                                                                                              |
|  | Appendix 1                                                                                                       | Blood collection volume for PK sampling and total estimated blood collection volume per subject revised down.                                          | Blood collection volume for PK sampling was revised to reduce total volume of blood required to be collected from each subject over the course of the study. |

### Appendix 5. Summary of Changes from Amendment 2 to Amendment 3

| Amendment   | Section                    | Changes                                                                                                                | Rationale                                                                                                                                                                              |
|-------------|----------------------------|------------------------------------------------------------------------------------------------------------------------|----------------------------------------------------------------------------------------------------------------------------------------------------------------------------------------|
| Amendment 3 | 5: Summary of Changes      | Section added                                                                                                          | Section was added to allow description of changes for the amendment.                                                                                                                   |
|             | Title Page                 | Added PI and medical monitor name and address                                                                          | Based on CRO selection                                                                                                                                                                 |
|             | Synopsis, Section 3.2,     | Revision to secondary objectives                                                                                       | since intermediate or poor metabolizers CYP3A4 are to be excluded.                                                                                                                     |
|             | Synopsis                   | Updated country of the trial                                                                                           | Based on CRO selection                                                                                                                                                                 |
|             | Section 4.1, Section 5.0   | Clarified wording for sample size calculations to plan to enroll a minimum of 60 subjects with at least 50 completing. | Revised enrollment numbers based on study size and power calculations which incorporated data from newly performed PK simulations and to incorporated endpoints based on FDA feedback. |
|             | Section 4.1.2,             | Revised timing for COVID-19 virus test                                                                                 | To meet the testing guidelines of CRO                                                                                                                                                  |
|             | Section 4.1.2              | Revised language in footnotes f and J                                                                                  | Text revised to clarify requirements                                                                                                                                                   |
|             | Section 4.3.2, Section 8.5 | Revised type of thermometer to be used, added temperature in Celsius scale                                             | Text revised to clarify requirements, country specific requirements                                                                                                                    |
|             | Section 5.1                | Split the inclusion criteria in two separate criteria
Revised wording
Added serology test                        | Text revised to clarify inclusion requirement
Text revised to clarify who can make decision
To screen patient with any abnormal tests                                            |
|             | Section 5.2                | Revised wording in criteria 11 and 16                                                                                  | Text revised to clarify requirements                                                                                                                                                   |
|             | Section 6.1.1              | Revised wording                                                                                                        | Text revised to clarify who can make decision                                                                                                                                          |
|             | Section 7.1.1              | Added French as requirement for IP label                                                                               | Text revised to clarify based on CRO site                                                                                                                                              |
|             | Section 7.3                | Revised wording                                                                                                        | Text revised to clarify who can make decision                                                                                                                                          |

|  |                                                      |                                                                |                                                                                                          |
|--|------------------------------------------------------|----------------------------------------------------------------|----------------------------------------------------------------------------------------------------------|
|  | Section 8.2                                          | Updated wording for subject identification number              | To meet the procedures and guidelines of CRO                                                             |
|  | Section 10.5.1                                       | Added wording for additional number of subjects to be enrolled | Based on interim pkanalysis number of subjects will be adjusted                                          |
|  | Synopsis, Section 4.1, Section 4.3.1, Section 5.25.2 | Changed screening window from 28 days to 45 days               | To screen sufficient number of subjects needed for trial                                                 |
|  | Synopsis, Abbreviations, Section 4.1                 | Defined Reference Listed Drug and Reference Substances         | To differentiate between Reference listed drug and available reference standard to be used in the study. |

#### Appendix 6. Summary of Changes from Amendment 3 to Amendment 4

| Amendment   | Section                                 | Changes                                          | Rationale                                                              |
|-------------|-----------------------------------------|--------------------------------------------------|------------------------------------------------------------------------|
| Amendment 4 | Summary of Changes                      | Section added                                    | Section was added to allow description of changes for the f amendment. |
|             | TOC, Section4.1.2.Table4.1, Section 4.5 | Changed screening window from 28 days to 45 days | Inadvertently was missed in earlier amendment..                        |
|             | Synopsis                                | Updated Inclusion Exclusion Criteria             | Based on wording in the main body of the protocol                      |

#### Appendix 7 Summary of Changes from Amendment 4 to Amendment 5

| Amendment   | Section                                                  | Changes                                                                                                  | Rationale                                                                                            |
|-------------|----------------------------------------------------------|----------------------------------------------------------------------------------------------------------|------------------------------------------------------------------------------------------------------|
| Amendment 5 | Synopsis                                                 | Participant duration in the study was changed from ~40 days to ~56 days                                  | Based on extended screening window                                                                   |
|             | Synopsis Inclusion criteria 13, Section 5.1, section 8.8 | Added blood test for genetic testing to identify metabolic genotype for CYP3A4                           | Due to on going Covid-19 pandemic buccal swabs are in short supply and thus blood test is added      |
|             | Synopsis Inclusion criteria 17, section 5.1              | Restriction on sperm donation for male subjects reduced to 30 days from 90 days to match with criteria15 | Based on literature information for nimodipine and similar class of compounds it was too restrictive |

|  |                |                                           |                                                                                                                    |
|--|----------------|-------------------------------------------|--------------------------------------------------------------------------------------------------------------------|
|  | Section 7.1.2  | Updated capsule in print to NM1 from H108 | Typographical error corrected to match the description on RS capsules                                              |
|  | Section 8.15.3 | Updated the wording and symbol            | To clarify the time the action needs to be taking for unplanned infusion interruptions and to match with table 8.2 |

#### Appendix 8 Summary of Changes from Amendment 5 to Amendment 6

| Amendment   | Section                                      | Changes                                                                                                 | Rationale                                                                                                                                     |
|-------------|----------------------------------------------|---------------------------------------------------------------------------------------------------------|-----------------------------------------------------------------------------------------------------------------------------------------------|
| Amendment 6 | Title page and footer of the document        | Updated the version and date of amendment.                                                              | Requested by CRO (Altasciences) due to Amendment 05 of the protocol being submitted to the IRB prior to receiving the NOL from Health Canada. |
|             | Synopsis, Section 4.1.2 Table 4.1 footnote J | Added serology test at screening only
Added Day 4 for Covid testing                                  | To clarify when serology test is to be performed
In order to be consistent with exclusion criterion 2                                      |
|             | Synopsis, Section 5.2                        | Revised exclusion criteria 20 from 90 days to 30 days                                                   | For consistency with inclusion criteria 17                                                                                                    |
|             | Table 6.1, Section 8.3                       | Corrected requirement for Experimental drug and/or experimental medical device from 3 months to 28 days | For consistency throughout the protocol as described in exclusion criterion 16                                                                |
|             | Section 8.11.1.1                             | Added 0.5 timepoints, blood samples for PK analysis                                                     | For consistency throughout the protocol as described in Table 4.1                                                                             |
|             | Section 8.15.3 and Table 8.2                 | Added language for how to manage infusion interruption                                                  | To clarify how interruption in infusion will be managed.                                                                                      |
|             | Table 8.1                                    | Deleted Covid test under serology                                                                       | Was inadvertently included under serology                                                                                                     |

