Note that for Figure 1-2, as in Figure 1-1, the  $C_{max}$  depicted here for the oral regimen does not correspond to the calculated  $C_{max}$ , as the time to  $C_{max}$  ( $T_{max}$ ) varies considerably between subjects for the oral dose (due to between subject variability in  $K_a$ ), but  $T_{max}$  is always exactly 0.5 hours for the IV formulation. Also of note is the reduced variability with the IV regimen due to the elimination of variability in BA and food effect, resulting in fewer concentrations greater than 100 ng/mL).

Based on the results of the modeling and simulations, the GTX-104 regimen most likely to be comparable to the NIMOTOP regimen was determined as a 30-minute infusion of 4 mg q4h and a continuous infusion of 0.15 mg/h such that the total drug infused over the first 30 minutes q4h equals 4.075 mg and the total drug infused every 4 hours equals 4.6 mg. This regimen is likely to match  $C_{max, Day 1}$  8 AM dose, and  $AUC_{Day 3, 0-24hr}$  for the reference formulation and regimen (NIMOTOP, 60 mg q4h) and result in similar geometric mean  $C_{max}$  for Day 3 (all six doses) for both regimens.

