### 1.3.2. Dose Justification

Based on popPK modeling and simulations, the GTX-104 IV dose regimen of a 4 mg dose administered over 30 minutes q4h in conjunction with 0.15 mg/h continuous infusion is likely to match  $C_{max}$  on Day 1 and  $AUC_{Day 3 0-24hr}$  for oral nimodipine q4h and result in similar  $C_{max}$  on Day 3 for both IV and oral regimens. Continuous infusions with GTX-104 at rates up to 1.4 mg/h for a day or more were demonstrated to be well tolerated in Study GTX-104-001. A literature review of studies with IV nimodipine administered at doses of up to 8 mg over 30 minutes suggest that the proposed 4 mg dose administered over 30 minutes does not represent a substantial clinical safety risk. Hypotension, as with all nimodipine treatments, is a potential concern; however, several factors facilitate managing the risk of hypotension with the IV regimen. These include:

1. The PK variability from the IV formulation is less than that from the oral regimen (Figure 1-2).
2. The distribution half-life of nimodipine is short (1 to 2 hours). As such, the plasma concentrations are expected to fall rapidly if hypotension required the infusion to be stopped. No option exists for stopping absorption following oral administration.

Overall, the proposed GTX-104 dosing regimen is anticipated to represent acceptable clinical safety and considered likely to match  $C_{max}$  and AUC for oral nimodipine q4h. Scheduled BP monitoring is included in the study to closely follow hypotension as a potential AE. Withdrawal criteria for subjects in the event of hypotensive events are described in Section 9.9.

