| Adverse events assessments                                           |                        |                 | ← Continuous →                     |                                                       |                                                  |                                                        |
| Concomitant medications                                              |                        |                 | ← Continuous →                     |                                                       |                                                  |                                                        |
| Clinic discharge                                                     |                        |                 |                                    |                                                       |                                                  | X                                                      |

CYP = cytochrome P450; EOS = End of Study; ET = Early Termination; FSH = follicle-stimulating hormone; hbA1c = hemoglobin A1c; ID = identification

- a. For treatment sequence AB, Treatment 1 will be Treatment A (GTX-104) and Treatment 2 will be Treatment B (oral nimodipine); for treatment sequence BA, Treatment 1 will be Treatment B (oral nimodipine) and Treatment 2 will be Treatment A (GTX-104).
- b. Each treatment period should be separated by a minimum of 96 hours to allow for treatment washout; washout time will be different for subjects, depending on their assigned treatment sequence (see Section 6.3).
- c. End of Study (EOS) assessments should be attempted in the event of Early Termination (ET). If the subject consents, this should include a blood sample for pharmacokinetic (PK) analysis taken as soon as possible after the decision to withdraw has been made.
- d. Overall Study Day may vary depending on the length of the washout period. The washout period should be at least 96 hours and adjusted such that the first dose administration of treatment 2 starts at approximately 8 AM.
- e. Confirmation of medical history and update, if needed.
- f. On Days 1 and 8 vital signs should be recorded within 1 hour prior to the first dose. On Days 3 and 10, blood pressure should be at 1 hour post-dose (for both IV and oral dose) for the 8:00 AM, 12:00 PM, 4:00 PM 8:00 PM doses. Measurements should be performed as described in Section 8.10. The same arm is to be used for all BP determinations.

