- g. Unless otherwise noted (i.e., Days 3 and 10, see “f” above), blood pressure measured approximately q12h while subjects are in-clinic or before collection of PK blood samples, as appropriate.
- h. Serum pregnancy test ( $\beta$ -human chorionic gonadotropin [ $\beta$ -hCG]) for female subjects of childbearing potential.
- i. COVID-19 virus test to be collected within 5 days of CRU admission.
- j. COVID-19 virus test to be collected in the morning of Day 4 and on Day 7 on admission, with results to be available by Day 8, start of Period 2.
- k. For postmenopausal female subjects.
- l. Human immunodeficiency virus (HIV), hepatitis C (HCV), and hepatitis B surface antigen (HBsAg); will be tested at Screening only.
- m. Based on subjects’ randomized treatment sequence (AB or BA) GTX-104 or oral nimodipine should be administered as described in Section 4.1.1 and Section 6.2. GTX-104 administration will be a 30-minute infusion of 4 mg every 4 hours (q4h) in addition to the continuous infusion of 0.15 mg/h; nimodipine capsules will be administered orally with 240 mL of water at a dose level of 60 mg (two 30 mg capsules) q4h for 72 hours. For Treatment A, the continuous infusion will be completed at 72 hours post-start of infusion (approximately 8 AM on the fourth day of the treatment period); no 4 mg dose will be given at 72 hours.
- n. Meals and water should be provided during dosing as described in Section 6.3.1.

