## **8.10. Blood Pressure Monitoring**

Monitoring and assessment of BP will be conducted by the study site per standard operating procedures.

For both Treatment A and Treatment B, BP will should be recorded via oscillometric sphygmomanometer at baseline (prior to first dose for both treatment arms) and 60 minutes post dose for the 8:00 AM, 12:00 PM, 4:00 PM, 8:00 PM doses on Days 3 and 10. The same arm is to be used for BP determinations will be used for all BP determinations with methods consistent with recommendations from the American College of Cardiology and American Heart Association ([Whelton et al., 2018](#)).

Baseline (prior to first dose, both treatment arms) assessment will occur within 1 hour prior to initiation of infusion or oral dose. Subjects will be placed in the same position to be used for drug administration, and the same arm to be used for BP determinations following dosing will be used for baseline BP determinations. The proper cuff size will be used, and the same cuff size will be used for all BP determinations associated with the current drug treatment. The arm is to be extended and supported at the same level as the heart. Three sequential BP determinations will be made within a 15-minute time span within 1 hour prior to drug administration. The baseline blood pressure will be the mean of the three BP determinations.

This procedure will be repeated with single measurements 60 minutes post dose on Days 3 and 10 for the 8:00 AM, 12:00 PM, 4:00 PM, and 8:00 PM doses. Subjects will be asked to refrain from strenuous activity for the duration of this assessment.

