| 
If the subject shows symptoms of hypotension and/or bradycardia (e.g., lightheadedness, dizziness, syncope, signs of hypoperfusion) regardless of the vital sign assessment.
 | 
If the subject shows symptoms of hypotension and/or bradycardia (e.g., lightheadedness, dizziness, syncope, signs of hypoperfusion) regardless of the vital sign assessment.
 
If the following vital sign assessments are observed pre-dose:
 
Resting (sitting or recumbent if necessary due to an AE):
 
 
• SBP <90 mmHg and >20 % below baseline value;
 
• DBP <50 mmHg and >20% below baseline value; or
 
• Heart rate <50 beats per minute and >20% below baseline value.
 
 
Orthostatic (after standing for 3 minutes):
 
 
• SBP, DBP, or heart rate >25% below sitting/recumbent values.
 
 | 
For all subjects: Inform subjects that nimodipine may cause hypotension and that moving from a supine to an upright position may increase risk for hypotension and orthostatic effects. Encourage subjects to stay hydrated. Offer fluids frequently. Monitor for symptoms of low blood pressure.
 
For all subjects with asymptomatic or symptomatic hypotension or who otherwise meet the dose hold criteria: Place subject on bed rest and encourage to drink fluids.
 
For asymptomatic blood pressure and heart values that meet one of the dose hold criteria: Repeat the vital sign assessment approximately 10 minutes later and if confirmed, hold the dose. If not confirmed with second assessment, take a third set of vital signs approximately 10 minutes later and hold the dose if confirmed in 2 of the 3 assessments.
 
For syncope or severe symptomatic hypotension: Monitor vital signs at least every 15 minutes until the subject is stable and able to resume normal activities.
 
Discontinue subject from study if any of the following criteria are met:
 
 
• Persistent signs or symptoms of hypotension, bradycardia, or hypoperfusion.
 
• Single occurrence of symptomatic bradycardia (as assessed by the Investigator, regardless of blood pressure) associated with chest pain, shortness of breath, or decreased level of consciousness.
 
• Any other clinically significant cardiovascular signs or symptoms that would place the subject at risk.
 
 |

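### Appendix 2 ties its vital-sign dose-hold thresholds to pre-dose values, but Table 4-1 schedules no pre-dose blood pressure for at least 6 to 7 of the 18 doses per period, and the 60-minute readings on Days 3 and 10 are not a stated trigger

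*Protocol*

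**What the plan says.** **The rule.** Protocol Section 9.9 applies the Appendix 2 criteria from the start of dosing. The dose-hold column has two parts:

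- A symptom part, which applies whatever the vital signs show.
- A vital-sign part, with thresholds for resting SBP, DBP and heart rate and for orthostatic change. These count "If the following vital sign assessments are observed pre-dose".

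Section 8.14 requires pre-dose assessments to be finished before the dose, but does not say how far back a value may lie and still count.

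**The schedule.** Three provisions in Table 4-1 and Section 8.10 set the on-treatment readings:

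- First dose of each period (footnote f): "On Days 1 and 8 vital signs should be recorded within 1 hour prior to the first dose".
- Other in-clinic time, with Days 3 and 10 excepted (footnote g): "blood pressure measured approximately q12h while subjects are in-clinic or before collection of PK blood samples, as appropriate". No clock time is given.
- Days 3 and 10 (Section 8.10): "This procedure will be repeated with single measurements 60 minutes post dose on Days 3 and 10", for the 8 AM, 12 PM, 4 PM and 8 PM doses.

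**The concern.** A threshold that counts only before a dose needs a reading before a dose. If the schedule does not provide one, that part of the rule has nothing to act on for that dose.

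The readings that are fixed on Days 3 and 10 have the opposite problem: they exist, but the rule does not name them. Take an asymptomatic SBP of 85 mmHg, more than 20% below baseline, found 60 minutes after a dose and confirmed on repeat. It meets no stated hold criterion unless it is treated as a pre-dose value for a dose three hours later.

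This bears on the protocol's own safety case. Section 1.3.2 names hypotension as the concern and relies on being able to stop the drug, since "the plasma concentrations are expected to fall rapidly if hypotension required the infusion to be stopped". The withdrawal criterion for hypotensive events in Section 5.4 also points to Appendix 2.

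**Working it through.** There is no stated figure for coverage to reproduce, so this is a direct count.

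**Inputs**

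- Doses (Section 6.3): every 4 h for 72 h, so 72 / 4 = 18, at 0, 4, …, 68 h. This matches the stated 18.
- PK samples (Section 8.11.1): 9 on Day 1 plus 49 from 48 to 72 h = 58 per treatment, and 2 × 58 = 116, as stated. Those falling at dose times are at 0, 4, 48, 52, 56, 60, 64 and 68 h. None falls on Day 2 (24 to 44 h).
- First-dose reading (footnote f): 0 h.
- 12-hourly readings (footnote g): clock time not given. They are assumed to coincide with doses, which favours the plan, and all three possible timings are tried.

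**Most favourable reading:** footnote f, the 12-hourly readings and a reading before every PK sample, ignoring the Days 3 and 10 exception.

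- 12-hourly from 0 h: uncovered doses at 8, 16, 20, 28, 32, 40 and 44 h, so 18 − 11 = 7.
- 12-hourly from 4 h: uncovered at 8, 12, 20, 24, 32, 36 and 44 h, so 7.
- 12-hourly from 8 h: uncovered at 12, 16, 24, 28, 36 and 40 h, so 18 − 12 = 6.

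That is 6/18 = 33% to 7/18 = 39% of doses. On Day 2, two readings serve six doses, so 4 of 6 are uncovered at every timing.

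**Stricter readings of footnote g** (doses uncovered, of 18):

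| Reading | From 0 h | From 4 h | From 8 h |
|---|---|---|---|
| PK clause used, exception ignored | 7 | 7 | 6 |
| PK clause used, exception covers 48 to 60 h | 11 | 11 | 10 |
| PK clause used, exception covers all six Day 3 doses | 13 | 13 | 12 |
| 12-hourly only, exception ignored | 12 | 11 | 11 |
| 12-hourly only, exception covers all six Day 3 doses | 14 | 13 | 13 |

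**A looser meaning of pre-dose.** Keep the most favourable schedule, let any scheduled reading in the 4 hours before a dose count (the 60-minute readings included), and let the 12-hourly series start at any whole hour. The count is still 6 to 7, with 4 of 6 uncovered on Day 2 throughout.

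**The 60-minute readings.** They fall at 49, 53, 57 and 61 h. Section 1.3 says that simulated Tmax "is always exactly 0.5 hours for the IV formulation", so in Treatment A they come 1 − 0.5 = 0.5 h after the expected peak and 4 − 1 = 3 h before the next dose. No section makes them a hold trigger.

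**The case against.** The strongest reply is that Appendix 2 is guidance to a physician. The hold is to be considered after the principal investigator's evaluation, and Sections 5.4 and 9.9 leave room for discretion. The symptom part works at any time. Bed rest and fluids apply to asymptomatic hypotension too, and subjects are discontinued for persistent signs of hypotension whether or not these were seen before a dose. Section 8.10 adds that "Monitoring and assessment of BP will be conducted by the study site per standard operating procedures", which could supply further readings. All of this stands. A reader might infer that a subject with a low 60-minute value is left unprotected; the document does not support that.

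It can also be said that by 60 minutes the high-rate infusion is over or the capsules are swallowed, so the value just before the next dose is the one that should decide. That is a fair point, and the fix keeps that value decisive. It does not explain how the value is obtained when no reading is scheduled and a low 60-minute result does not prompt one.

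Three further inferences should not be drawn:

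- **That heart rate goes unmeasured.** Footnotes f and g belong to the vital-signs row of Table 4-1, and Section 8.5 includes pulse rate among vital signs.
- **That the repeat intervals in Section 8.5 and Appendix 2 conflict.** Section 9.9 puts the Appendix 2 criteria in force once dosing starts, and the Section 8.5 repeats are optional.
- **That the orthostatic threshold can never be used.** Section 8.6 schedules orthostatic tests only at Screening and Day -1, but in an event-management table the natural reading is a check done for cause. A clarifying phrase would be enough.

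**Conclusion.** The mismatch is real. A stated safety rule lacks its scheduled input for about a third of doses or more: 6 to 7 of 18 per period at best, and up to 14 on the strictest reading of footnote g. It also gives no hold response to a confirmed asymptomatic low value at 60 minutes. The Day 2 figure of 4 in 6 does not depend on how the exception is read.

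The counts assume 12-hourly readings timed at doses and no extra readings under site procedures, which are not shown. They measure scheduled coverage. The document gives no basis for turning them into an expected number of missed hypotensive events. Given the other protections, the severity is minor to moderate.

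**What to change.** 1. In Appendix 2, replace the pre-dose condition with *observed at any on-treatment reading, including the 60-minute post-dose reading*. Keep the existing confirmation (repeat after about 10 minutes, 2 of 3). For a confirmed low value, require a recheck immediately before the next dose, and hold that dose if the value is still below threshold.
2. In Table 4-1 footnote g, time the existing 12-hourly readings just before a scheduled dose.
3. As a wording note, state that the orthostatic threshold applies to checks done for cause.

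**Cost.** No new scheduled readings are needed; a recheck follows only a confirmed low value. There may be more holds. This matters most in Treatment A, because Section 9.9 discontinues a subject whose infusion is stopped on these criteria and the design needs 50 completers. The pre-dose recheck limits that by keeping brief dips after the peak from leading to a hold.

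Adding a cuff reading before every uncovered dose is not proposed. Some would fall at night, and Appendix 4 records that the blood pressure schedule was revised for the unit's logistics, so that is a trade-off for the sponsor and the site.
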